## 5. STUDY DESIGN

### 5.1. An integrated study design

This clinical study combines a clinical safety evaluation of the CVR with social science research on acceptability and adherence of ring use in Rwandan women.

The *clinical part* of the study assesses the general safety of the contraceptive ring including the effect on the vaginal microbiome, genitourinary symptoms and signs and clinical adverse events. In addition the *clinical part* of the study aims to understand better the possible biofilm formation and to explore the impact of the ring on the microbiome and inflammation in the vagina.

The *social science component* consists of a combination of qualitative and quantitative research including IDIs, FGDs, questionnaires, and (if funding permits) audio computer-assisted self-interviewing (ACASI).

### 5.2. Clinical study design

This is an open label single-centre cohort study with the NuvaRing®. A total of 120 HIV-negative women will be randomized to an intermittent regimen or a continuous regimen of ring use and will be followed for maximum 14 weeks, to determine general safety of the ring in the African context, and to determine differences in the vaginal microbiome and vaginal inflammation before and after use of a CVR. Qualitative research for the social science component will be performed to address the acceptability and adherence of intermittent or continuous CVR use in more depth.

Women will be randomized into two study groups: 60 intermittent users in group A and 60 continuous users in group B. Both groups will use the NuvaRing®. Women in group A (the intermittent users) will use each CVR for 3 weeks followed by one week of no ring use to allow menstruation. Women in group B (the continuous users) will use each ring for 3 weeks, with the next ring being inserted immediately after the previous one and no off period in between [4]. The total duration from enrolment to the last study visit is maximum 14 weeks. The screening process will be a maximum of 6 weeks.

#### *Schedule*

[figure not shown]

## 6. STUDY OBJECTIVES AND ENDPOINTS

| Study Method             | Primary objectives                                                                                                                  | Primary endpoints                                                                                                                                                                                                                                                                                                                                                                                                                                                                                       |
|--------------------------|-------------------------------------------------------------------------------------------------------------------------------------|---------------------------------------------------------------------------------------------------------------------------------------------------------------------------------------------------------------------------------------------------------------------------------------------------------------------------------------------------------------------------------------------------------------------------------------------------------------------------------------------------------|
| Clinical Trial           | To assess the impact on the vaginal microbiome of the use of a CVR intermittently (3 weeks followed by 1 week off) or continuously. | Changes from baseline (pre-ring use) in vaginal bacterial counts and in the absence/presence of BV-related bacteria as measured with quantitative real time PCR.                                                                                                                                                                                                                                                                                                                                        |
| Social Science Component | To assess the level of acceptability and reported adherence to intermittent and continuous CVR use in women in Rwanda.              | Lost to follow up rate; rate of discontinuation (base on clinical trial data).
Level of adherence based on self-reported adherence scale and diary cards.
Qualitative description of user experiences, relationship attributes, and sexual encounter attributes.
Reported vaginal practices and beliefs regarding menstruation and impact on ring adherence.
Reported reproductive health symptoms and impact on adherence.
Number of women envisaging future use of contraceptive ring. |
| Study Method             | Secondary objectives                                                                                                                | Secondary endpoints                                                                                                                                                                                                                                                                                                                                                                                                                                                                                     |
| Clinical Trial           | To assess the general safety of the CVR.                                                                                            | Incidence of self-reported vaginal symptoms and clinician-observed signs
Incidence of BV.
The numbers of women prematurely withdrawing from the study or discontinuing ring use.
Incidence of adverse and serious adverse experiences .
The numbers of incident STIs and candidiasis.
Nugent scores and Ison & Hay grading of the vaginal flora.                                                                                                                                         |
| Clinical Trial           | To assess the vaginal biofilm formation according to ring use regimen.                                                              | Changes in phenotype of BV-related bacteria, specifically:
- Presence of dispersed forms of bacteria;
- Presence of adhesive forms of bacteria on epithelial cells.                                                                                                                                                                                                                                                                                                                               |
| Clinical Trial           | To determine the presence or absence of a biofilm on the CVRs after intermittent or continuous use by visualization of the biofilm. | Presence or absence of a biofilm on the CVRs after intermittent or continuous use:
- Presence of biofilm visualized by crystal violet;
Visualization of adherent bacteria using FISH;
- Identification of adherent bacteria (including but not limited to Lactobacilli sp., G. vaginalis , A. vaginae ).                                                                                                                                                                  |

| Study Method      | Secondary objectives (cont.)                                                                                                        | Secondary endpoints (cont.)                                                                                                                                                                                                                                                                                                                                                                     |
|--------------------------|--------------------------------------------------------------------------------------------------------------------------------------------|--------------------------------------------------------------------------------------------------------------------------------------------------------------------------------------------------------------------------------------------------------------------------------------------------------------------------------------------------------------------------------------------------------|
| Clinical Trial           | To assess the impact of CVR on vaginal inflammation and immune activation according to ring use regimen.                                   | Changes in inflammatory cytokines concentrations in CVLs as measured by Luminex technology. The cytokines analyzed include, but are not limited to IL-1, IL-6, IL-8, IL-10. All samples that are showing elevated cytokine levels, as well as an equal number of controls not showing elevated cytokine levels, will be tested further for the presence of proteins involved in inflammatory pathways. |
| Social Science Component | To identify and describe the context specific attitudes and beliefs regarding family, FP, and gendered norms.                              | Qualitative description regarding women's views on family structure, family planning methods, sexuality, and community norms and perceptions regarding FP and sexuality.                                                                                                                                                                                                                               |
| Study Method      | Exploratory Objectives                                                                                                              | Exploratory endpoints                                                                                                                                                                                                                                                                                                                                                                           |
| Social Science Component | To explore the women's beliefs and expectations regarding future potential use of a multi-purpose ring (contraception and HIV prevention). | Qualitative descriptions of beliefs, attitudes, and expectations regarding multi-purpose rings.
Number of women reporting likelihood of future use of multi-purpose ring.                                                                                                                                                                                                                           |
| Social Science Component | To explore how women and men in Rwanda perceive and experience risk related to unwanted pregnancy and HIV.                                 | Qualitative description of perceived risk of HIV and unwanted pregnancy and personal experiences of risky situations.                                                                                                                                                                                                                                                                                  |

## **7. SUBJECTS, POPULATION & SELECTION**

### **7.1. Settings, selection & recruitment**

A total of 120 HIV-negative women will be recruited from the general population. They will receive extensive counselling on all contraceptive methods that are available in Rwanda. Women will also be counselled on prevention of HIV and other STIs, and will be offered HIV and STI testing and condoms free of charge. The social science component of the acceptability study will include IDIs and FDGs and these will take place alongside the clinical study.

All participants will be recruited and followed up at the Rinda Ubuzima (RU) research clinic and laboratory in Kigali, Rwanda. Rinda Ubuzima (formerly Projet Ubuzima) was established in 2004 and has successfully conducted 7 clinical studies in the areas of HIV prevention and reproductive health between 2004 and 2012, including two clinical trials with an experimental vaginal microbicide. Rinda Ubuzima receives technical assistance in all of its studies from the University of Liverpool (UoL), Institute of Infection and Global Health.

The following sections describe the groups and the inclusion and exclusion criteria in detail.

### **7.2. Inclusion and exclusion criteria**

In order to be eligible, study participants **must meet the following criteria**:

- » Able and willing to give informed consent/assent, according to national guidelines
- » Female who self-reports to be sexually active (meaning at least one penetrative vaginal coital act per month for the last 3 months prior to screening)
- » Between 18 to 35 years old, inclusive
- » Currently in good physical and mental health
- » Interested in initiating hormonal contraception
- » Able and willing to participate in the study as required by the protocol, this includes willing to undergo HIV testing and use a NuvaRing®
- » HIV negative at screening as confirmed by rapid HIV testing

Potential participants meeting any of the following criteria **will not be enrolled in the study**:

- Currently using a modern contraceptive method other than barrier methods
- Use of a hormonal contraceptive method in the three months prior to the screening visit
- Currently using antimicrobial medication
- Pregnant on urine pregnancy test
- History of cardiovascular disease
- History of hysterectomy or genital tract surgery (including cervical polypectomy, dilatation and curettage, hysteroscopy, or laparoscopy) in the three months prior to the screening visit

- History of complications with hormonal contraception or with contra indications for the use of hormonal contraceptives such as:
  - History or known predisposition for venous thrombosis
  - History of migraine with focal neurological symptoms
  - Diabetes mellitus with vascular involvement
  - History of pancreatitis or severe hepatic disease
  - Known or suspected hypersensitivity to any of the excipients of NuvaRing®
- History of significant urogenital or uterine prolapse, undiagnosed vaginal bleeding, incontinence or urge incontinence, diagnosed chronic and/or recurrent vulvovaginal candidiasis, urethral obstruction
- Participating in other clinical studies involving investigational products
- Currently breastfeeding
- Currently a smoker

### **7.3. Sample size**

A total of 120 women will be enrolled in the clinical trial: 60 women will be randomized to the intermittent regimen of ring use and 60 women to the continuous regimen of ring use. This will ensure we have 104 women with evaluable primary outcome data to provide sufficient power for the primary clinical trial objective. This is based on the sample size calculations presented in protocol section 11.1.3.

As is always the case in qualitative research, sample sizes are determined by when data saturation is reached (meaning: additional IDIs or FGDs do not generate new information that was not already mentioned in previous IDIs or FGDs). In this study protocol, we list estimates (based on our experience with previous qualitative research) of how many IDIs or FGDs are needed to reach data saturation, but fewer or more IDIs or FGDs may be done based on the actual results when we are implementing the study.

After pre-screening, IDIs will be conducted until data saturation is reached, which we assume to be the case after interviewing 10-15 women. Midway through the project, two FGD per randomization group will be conducted including 8-12 women per FGD (for a total of 32 to 48 women in 4 FGDs). At the end of the trial, one FGD (with 8-12 women per group) and 3-5 IDIs per randomization group will be conducted (for a total of 16-24 women and 6-10 women, respectively). Women participating in the end of trial FGDs and IDIs will be invited to ask their male partners to attend separate IDIs and 3-5 male partners will be interviewed in each randomization group (for a total of maximum 10 men). Additional FGD will be conducted with women who are not enrolled in the clinical study (8-12 women per FGD) until data saturation is reached: at least one FGD with women who attend a family planning clinic and at least one FGD with women who are HIV-positive.

## **7.4. Randomization and blinding**

This is an open-label study because the differences in ring use (intermittent or continuous use) cannot be blinded. Individual participants will be randomized and treatment allocation will be concealed until a participant has provided informed consent, confirmed eligible, and is included in the study. Randomization will be done at enrolment using randomization envelopes, specifying the treatment group.

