- The pelvic and general physical examinations will be performed as at baseline. A total of 3 vaginal swabs are collected for:
  - One cotton swab for Wet Mount [*Trichomonas vaginalis* (TV); *Candida albicans*] and smears for BV diagnosis;
  - Two regular flocked swabs (Copan, Italy) for the characterisation of the vaginal microbiome.
- At visit 6 for Group A and visit 5 for Group B, after the final ring has been removed and all other vaginal specimens have been collected, a CVL sample will be collected.
- A urine sample is obtained, tested for pregnancy and an aliquot of fixated urine will be stored for FISH analysis.
- A completed diary card will be collected at each visit and a new diary card will be provided. Any problems with ring use will be addressed.
- The removed ring will be processed according to the instructions provided by the ITM and stored for biofilm analysis.
- Risk reduction counselling will be provided as well as condoms (free of charge).
- During the last ring removal visit (V6 for group A and V5 for group B) the following additional procedures will be offered:
  - a Visual Inspection with Acetic acid (VIA) to identify women at risk for cervical cancer;
  - An HIV test according to the national HIV algorithm. A maximum of 5 ml of blood will be collected by venepuncture in a serum tube. Pre- and post-test HIV counselling will be provided.

Additional questionnaires during ring removal visits:

1. The IAQ will be performed at every visit and will assess adherence and acceptability of the ring use but will be more comprehensive at visits 4 and 6 for group A and at visits 3 and 5 for group B. It will also assess factors that might influence the vaginal microbiome and vaginal inflammation.
2. Between weeks 7 and 9, 16-24 women will be enrolled in one of two FGD in each randomization group, for a total of four FGD.

3. At the last ring removal visit, and if funding permits, all study participants will be invited to provide their feedback on experiences with the new contraceptive method, on acceptability and adherence using ACASI.

The following procedures are performed at the ring insertion visits for group A:

- Information on adverse events, social harms and concomitant medication will be collected.
- Risk reduction counselling will be provided as well as condoms (free of charge).

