### **8.4.1. Research laboratory procedures at RU or in other laboratories in Rwanda**

The following research tests will be performed at the RU laboratory:

1. A vaginal smear will be used for BV diagnosis and a microscopic description of the vaginal flora. The current gold standard for BV diagnosis in research settings is the Nugent score. This method relies on the semi-quantification of the bacterial morphotypes observed in a vaginal smear after Gram staining. The modified Ison & Hay grading is another system to describe the vaginal flora and provides more details on the *Lactobacillus* species compared to the Nugent score. The Nugent score will be used to diagnose BV and offer treatment to the women, whereas the modified Ison & Hay grading will be used for research purposes only.
2. Luminex cytokine testing will be used to identify women who have vaginal inflammation. All samples that are showing elevated cytokine levels, as well as an equal

number of controls not showing elevated cytokine levels, will be tested further for the presence of proteins involved in inflammatory pathways.

3. An additional cervical swab will be taken at baseline for the rapid detection of CT using the BioChekSwab; a rapid self-contained, two step enzyme detection system. The test will be evaluated by comparing results obtained by this rapid test with the results obtained by the CT/NG molecular technique.

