#### **8.4.2. Research laboratory procedures at ITM**

During the study, vaginal swabs, urine samples and the processed vaginal rings will be shipped to the STI reference laboratory at ITM for further testing:

1. Vaginal swabs will be tested with molecular amplification techniques for the characterization and quantification of the vaginal microbiome. Smears and an aliquot of the urine samples will be fixated and shipped to ITM to study the changes in phenotype of BV-related bacteria (from dispersed forms to adhesive forms on epithelial cells) to identify biofilm formation. Dispersed and adherent bacteria will be assessed in a multicolour analysis with a mix of differently stained group-specific and universal bacterial probes and visualized by confocal imaging.
2. The biofilms formed on the CVRs will be visualized using crystal violet staining and FISH, additional techniques may be applied if funding permits.

The shipment of the samples will be arranged by a regular courier by the laboratory administrator after proper preparation. Biological materials will be prepared and shipped in compliance with any applicable legislations and a Material Transfer Agreement (MTA).

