### 11.1.2.3. Primary analysis

The primary analysis is based on the qPCR vaginal flora data. This data comprises different species and is recorded at baseline (week 0), and at 3 (group A) or 4 (group B) time points during CVR use.

The presence/absence of each species during CVR use will be analyzed using repeated measures logistic regression models, with random intercepts and random slopes over time for each woman and fixed effects for randomization group (intercept and slope).

For species which are present in the vaginal microbiome of the majority of women and remain present throughout the study, mixed-effects linear regression models will be fitted on the log-transformed bacterial counts. As in the logistic regression models, random intercepts and random slopes over time for each woman and fixed effects for randomization group (intercept and slope) will be included in the linear regression model.

In addition, overall counts of different species may be pooled (e.g., of all *Lactobacillus* species, or all *Lactobacillus* species excluding *L. iners*) and analyzed using mixed-effects linear regression. As an alternative approach, a principal component analysis (PCA) will be performed on the qPCR data and the PCA scores analyzed using mixed effects linear regression. It is expected, based on preliminary analyses of previous dataset, that the first principal component of the flora composition may indicate a gradient from a healthy to a less stable microflora. Changes in the scores for this principal component may consequently indicate deleterious changes in the microbiome. Changes in the second and third principal component will also be explored if they appear to have a reasonable interpretation.

Effects over time will be described as odds-ratio's or changes in log-counts over each 4 week period together with 95% confidence intervals. Effects of the randomization group will be tested at the 5% level (two-sided).

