#### **11.1.3. Sample size and power**

The clinical study sample size calculation is based on the primary objective to assess the pre-post changes in the vaginal microbiome. We require 95% power to detect clinically important changes in bacterial counts. Preliminary analyses of our on-going biomarkers study showed a difference of (-)1 log in overall *Lactobacillus* sp. counts and of (+)3 log in *G. vaginalis* counts between participants with and without BV as assessed by Nugent score, and standard deviations of 1 and 3 for changes in overall *Lactobacillus* sp. counts and *G. vaginalis* counts, respectively. We have defined a change in bacterial count of 50% of the observed differences between women with and without BV as clinically important. Given this, we require 52 women in each study group. To correct for early withdrawals and women lost-to-follow up, we will randomize 120 women (60 in each study group) to ensure we have 104 women with primary endpoint data available.

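### Section 7.4's reason for an open-label trial does not cover the laboratory readers of smears, FISH preparations and stained rings, and no section masks them

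*Protocol*

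**What the plan says.** Section 7.4 gives one reason for having no blinding: "This is an open-label study because the differences in ring use (intermittent or continuous use) cannot be blinded". The only protection it adds comes before treatment starts: "treatment allocation will be concealed until a participant has provided informed consent, confirmed eligible, and is included in the study".

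Several outcomes compared between regimens are visual readings made in a laboratory:

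- **Nugent score (section 8.4.1, read at the site laboratory):** "This method relies on the semi-quantification of the bacterial morphotypes observed in a vaginal smear after Gram staining". The modified Ison & Hay grading describes the same vaginal flora. The Nugent result also determines who is offered treatment for bacterial vaginosis.
- **Dispersed or adherent bacteria (section 8.4.2, read at ITM):** assessed by FISH with confocal imaging.
- **Ring biofilm (section 8.4.2, read at ITM):** "The biofilms formed on the CVRs will be visualized using crystal violet staining and FISH".

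In section 11.1.1 these supply secondary endpoints 2 (incident BV), 6 (Nugent and Ison & Hay), 7 (bacterial phenotype) and 8 (ring biofilm). The primary endpoint is measured by qPCR.

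Sections 8.1.3 and 8.1.8 tie sampling to ring removal, and visits are numbered differently in the two arms. The final removal, for example, falls "At visit 6 for Group A and visit 5 for Group B".

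**The concern.** The impossibility of hiding a ring schedule from the woman who follows it says nothing about a Gram smear, a fixed urine aliquot or a removed ring. Each ring is worn for 3 weeks in both groups (section 5.2), and nothing in the protocol suggests that a specimen itself shows its arm. The readers could therefore be masked, but the section on blinding does not mention them.

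Masking would also not arise by default. Some visit numbers exist as sampling visits in one arm only, so a routine label with participant and visit number would disclose the regimen for part of the material.

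What is at stake is a shift in borderline calls that runs in one direction and looks like a regimen effect. Biofilm formation is named in the study's first aim. Section 11.1 says that the analyses for secondary objectives 2 and 3 will have no prior statistical analysis plan, so masked reading would be one of the few safeguards for the biofilm results.

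**Working it through.** **The plan's own sample size.** With a change of 0.5 log, SD 1 (or 1.5 log, SD 3), two-sided 5% and 95% power (section 11.1.3), the within-group pre-post formula gives n = ((1.960 + 1.645) x 1 / 0.5)^2 = 51.98, so 52 per group. This reproduces the stated figure. Masking readers does not change it; 52 serves below only as the number of evaluable women per arm.

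**Which samples show the arm.** Inputs: "60 intermittent users in group A and 60 continuous users in group B" (section 5.2) and the schedule in section 8.1.8, with full attendance.

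| | Group A | Group B |
|---|---|---|
| Ring-removal visits | V2, V4, V6 | V2, V3, V4, V5 |
| Nominal weeks | 4, 8, 12 | 4, 7, 10, 13 |
| Sample sets | 60 x 3 = 180 | 60 x 4 = 240 |
| Visit numbers sampled in this arm only | V6: 60 | V3, V5: 120 |

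- Total on-ring sets: 180 + 240 = 420.
- Arm shown by visit number: 60 + 120 = 180, and 180/420 = 43%.
- Arm not shown by visit number (V2, V4): 240/420 = 57%.
- Arm shown by nominal study week: only week 4 is shared, so 420 - 120 = 300, and 300/420 = 71%.

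Baseline samples precede randomization and show nothing.

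**What a reader shift would do.** The protocol gives no figure for reader bias, so these are assumptions: a true presence rate of 30% in both arms; a shift s of 5, 10 or 15 points in group B readings whose arm is known; within-woman correlation (ICC) 0.3 to 0.5. Readings: 52 x 3 = 156 in A and 52 x 4 = 208 in B.

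- Variance inflation 1 + (m - 1) x ICC: at ICC 0.3, 1.6 in A and 1.9 in B; at ICC 0.5, 2.0 and 2.5.
- Effective readings: 156/1.6 = 97.5 and 208/1.9 = 109.5; or 156/2.0 = 78 and 208/2.5 = 83.2.
- Spurious difference d = f x s, where f is the share of group B readings shifted (V3 and V5 only: 2/4 = 0.5; all: 1).
- False-positive rate = Phi(d/SE - 1.96) + Phi(-d/SE - 1.96).

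Example with s = 10 points, f = 0.5, ICC 0.3: d = 0.05; SE = sqrt(0.30 x 0.70/97.5 + 0.35 x 0.65/109.5) = 0.065; d/SE = 0.77; rate = Phi(-1.19) + Phi(-2.73), about 12%.

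| Group B readings shifted | 5 points | 10 points | 15 points |
|---|---|---|---|
| V3 and V5 only | 6-7% | 10-12% | 17-21% |
| V3, V4 and V5 (only V2 masked) | 8-9% | 17-21% | 32-40% |
| All | 10-12% | 27-33% | 51-62% |

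The lower end of each range is ICC 0.5. As a cross-check with one reading per woman (52 per arm, Fisher's exact test, base rate 20-40%, every group B reading shifted), the rates are about 3% with no shift, then about 6%, 14-16% and 29-32%.

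**The case against.** The strongest reply is that the protocol is silent here and has not decided against masking. It never says that readers will know the regimen, and it does not say what specimen labels carry. Section 12.1 refers laboratory conduct to SOPs and an analytical plan that are not shown. Participant numbers are assigned at pre-screening, before randomization (section 8.1.1.1), so they need not encode the arm, and the FISH and ring readings are made at ITM, away from the clinic. This stands: the supportable statement is that reader masking is not provided for in the protocol, not that readers are known to be unmasked.

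A reader might also infer three stronger things:

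- **That visit numbers alone give the regimen away.** They do so for V3, V5 and V6. V2 and V4 are sampling visits in both arms; a sample from them shows its arm only if it is linked to the same woman's other samples or carries a date.
- **That the trial's main result is at risk.** qPCR is an instrument measurement. An indirect path exists, because the Nugent reading leads to treatment offers, but the direct exposure is secondary. Endpoints 7 and 8 belong to analyses that the protocol itself calls data driven, so a 5% error rate is an illustration for them and not a planned confirmatory quantity.
- **That masking would be free.** The protocol says nothing on cost. Nugent results are needed at the site for care, while the data manager sits at the CTU (section 13.1), so a key held only there could delay them.

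None of this supplies a reason to leave the readers out of section 7.4.

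**Conclusion.** The point holds as a cheap improvement. The stated reason for open label does not extend to the smear, FISH and ring-biofilm readers, and the protocol does not mask them.

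If labels show visit numbers, the arm is visible for 43% of on-ring sample sets, and for more if samples are linked within a woman or dated. Under the assumed shifts, the V3/V5-only row of the table is the appropriate central illustration. The all-readings row is an upper bound that requires the arm to be known for every group B sample. The size of any shift, the base rate and the correlation are all assumptions.

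The exposure is confined to secondary endpoints 2, 6, 7 and 8, apart from the indirect route through treatment offers. If the laboratory SOPs already provide for masking, section 7.4 needs only to say so.

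**What to change.** - State in section 7.4 that the regimen is open to participants and clinic staff, and that the readers of Nugent and Ison & Hay smears, FISH preparations and ring biofilm are masked to it.
- Label these specimens with a code that shows neither group, visit number nor date, and have the planned readers work from the code alone.
- Merge allocation with the readings only after the laboratory databases are closed. Sections 8.3.1 and 13.1 already keep batched laboratory results separate until the end of the study.
- Have a person at the site who is not a reader hold the key for Nugent slides, so that results return to the clinic for care without delay. The data manager holds the key for specimens read at ITM.

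The cost is a small amount of labelling and key-handling work, with matching text in the laboratory SOPs. No extra reader, procedure or participant is needed.
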